## Abstract

**Background:**

Reablement is a promising new rehabilitation model, which is being implemented in some Western countries to meet current and future needs for home-based services. There is a need for further investigation of the effects of reablement among community-dwelling adults in terms of clinical and economic outcomes. This study will investigate the effectiveness of reablement in home-dwelling adults compared with standard treatment in terms of daily activities, physical functioning, health-related quality of life, coping, mental health, use of health care services, and costs.

**Methods/Design:**

The study is a multicenter controlled trial. In total, 44 Norwegian municipalities will participate, including eight municipalities as a control group. For three municipalities with two zones, one will be assigned to the control group and the other to the intervention group. The experimental group will be offered reablement and the control group standard treatment. The sample will comprise approximately 750 participants. People will be eligible if they are home-dwelling adults, understand Norwegian, and have functional decline. Participants will be assessed at baseline, and after 10 weeks, 6 months, and 12 months. The primary outcome will be activity and participation measured by the Canadian Occupational Performance Measure. Physical functioning will be measured by the Short Physical Performance Battery and health-related quality of life by the European Quality of Life Scale. Coping will be measured by the Sense of Coherence questionnaire and mental health by the Mental Health Continuum Short Form. Costs will be generated based on registered working hours in different professions. Data analyses will be performed according to intention to treat. Univariate analysis of covariance will be used to investigate differences between the groups at baseline and the end of intervention. The data will be organized into two levels using a multilevel structure, i.e., individuals and municipalities, which will be analyzed using linear mixed-effects models. The working hours data (panel data) will be analyzed with random mixed-effects regression models. The cost-effectiveness of reablement will be evaluated according to the incremental cost-effectiveness ratio and uncertainty will be explored via the bootstrap method.

**Discussion:**

The findings will make an important contribution to knowledge of rehabilitation approaches for community-dwelling adults.

**Trial registration:**

The trial was registered at ClinicalTrials.gov on October 24, 2014, identifier: NCT02273934.

## Background

Similar to many countries around the world, the Norwegian population is ageing [1]. As more people get older, many will require assistance in order to age in place as well as to be active and participate in society. Combined with an expected shortage of health care personnel, this situation will present a challenge to the health care system in years to come [1], which has increased interest in rehabilitation services. Reablement has become an emerging model in the rehabilitation services for community-dwelling older adults experiencing functional decline [2]. The overall aim of this model is to promote everyday competence and independent functioning in daily activities among home-living people in need of rehabilitation.

Reablement is an intensive, multidisciplinary, multicomponent, person-centered, home-based type of rehabilitation, where ordinary activities of daily living are used for rehabilitative purposes [3]. The main focus is on enhancing the performance of activities that are perceived as significant and meaningful in the daily life of each individual where health care providers are organized into multidisciplinary teams, which work together with the person toward their activity goals. The intervention is intensive and occurs in the person’s home or local community.

The outcomes in terms of the effects of reablement comprise individual health outcomes, health care service utilization, and cost-effectiveness. For individual health outcomes, the effects of reablement on the performance of personal activities of daily living (PADL) have been summarized in a systematic review [4], where the authors concluded that there is limited evidence that reablement can reduce the dependency of home-care service users during PADL. However, the results of primary studies are inconsistent. In some studies, the results showed that reablement improved instrumental activities of daily living [5–7], safety [7], physical function [6–8], and health-related quality of life (HRQoL) [9, 10], whereas others found no significant improvements in safety [5], social support [8], physical function [5], or HRQoL [5, 7].

In terms of health care service utilization, the results of a recent study showed that the participants in a reablement group required fewer home care hours, were less likely to be approved for a higher level of aged care such as nursing homes, and less likely to be in need of emergency department treatment compared with participants in a conventional care group [11]. It was also shown that people who received reablement were less likely to need personal care services [5, 12] and to be readmitted into hospital [3]. Thus, these results indicate that reablement may reduce the need for home care and other health care services.

The results are conflicting regarding the cost-effectiveness of reablement. In particular, there were no significant differences between the groups in terms of cost savings in a large clinical controlled trial [10], but the results of two other studies showed that the health and home care costs of reablement were lower than the costs of conventional home care [11, 12].

In summary, there has been insufficient research into the effects of reablement, and the results of research based on individuals and cost outcomes are inconsistent. Therefore, more research is needed to increase our knowledge of the effects of reablement.

### Purpose and research questions

The main aim of this study will be to investigate the health effects and cost-effectiveness of reablement compared with standard treatment in home-dwelling adults experiencing functional decline. The following research questions are posed.What is the effect of reablement on performance and satisfaction with performance of daily activities in home-dwelling adults?What is the effect of reablement on HRQoL and physical functioning among home-dwelling adults?What is the effect of reablement on coping as a sense of coherence and positive mental health among home-dwelling adults?What is the cost-effectiveness of reablement compared with standard treatment?

## Methods/design

### Design and setting

This will be a large multicenter clinical controlled trial. The study will be conducted in primary care settings in 44 of the 428 Norwegian municipalities, including eight municipalities that function as a control group; for three municipalities with two zones, one will be assigned to the control group and the other to the intervention group (see Fig. 1 for flow diagram). The allocation of zones to the intervention or control group was based on practical reasons and decided by the municipality. The municipalities included represent 17 % of the total population in Norway. The experimental group will be offered reablement and the control group standard treatment. The sample will comprise approximately 750 participants, who will be assessed at baseline and after 10 weeks, 6 months, and 12 months.

**Fig. 1 Fig1:**
[figure not shown]
Flow diagram showing the study protocol. *Three municipalities are each divided into two zones, where one zone acts as a control group and the other as an intervention group

The protocol follows the Standard Protocol Items: Recommendations for Intervention Trials (SPIRIT) 2013 statement [13], which defines standard protocol items for clinical items, and it has been registered with ClinicalTrials.gov (October 24, 2014, identifier: NCT02273934).

### Participants and eligibility criteria

People will be eligible if they are home-dwelling, over 18 years of age, understand Norwegian, and have experienced a functional decline. Participants will be excluded if they are in need of institution-based rehabilitation or nursing home placement, terminally ill, or cognitively reduced. The inclusion criteria are not restricted to older adults, but it is expected that this age group will comprise the majority of participants.

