### Interventions

#### Reablement

Reablement is an intensive, interdisciplinary intervention. In general, the intervention lasts for a period of 3–10 weeks. To enable and enhance activity performance, it is crucial to acknowledge that the person is the expert on her/his own life. The main focus is to establish a dialog to identify activities that the individual perceives as meaningful to work on or to improve. The intervention is targeted to achieving these activity goals. Therefore, the patient-specific Canadian Occupational Performance Measure (COPM) will be used as part of the baseline assessments to give directions for the modeling of the reablement intervention. The COPM interview and scoring start with the following question: “What are the most important activities in your life now?” During the COPM assessment, the participant will define up to five activity goals that are essential to her or him. Based on these goals, a rehabilitation plan will be developed to promote a match between the activities and goals identified by participants, and professional initiatives. Intensive attention will be given to encourage participation and stimulate daily training for the participants, including performing their daily tasks. Individual tailoring is a major principle of reablement, so the content of the intervention will vary among participants, although the basic features are the same. Table 1 gives an overview of the content of the intervention, including fundamental principles and key components.

**Table 1 Tab1:** Content of the reablement intervention

Fundamental principles	Process, key components
• The rehabilitation period will be a maximum of 10 weeks.	• *Training in daily activities* such as personal hygiene, climbing stairs, family visits, cleaning the house, being able to write, or walking indoors/outdoors.
• A person-centered, resource-oriented, and interdisciplinary approach will be applied.	

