#### The control intervention: standard treatment

The control group will receive standard treatment. In contrast to reablement, the standard treatment will not be time limited and thus it may continue after 10 weeks. Standard care often comprises compensating help and the content of the compensating help will be delivered according to the applications made by the participants. This may be personal or practical assistance, meals on wheels, safety alarm, or assistive technology. However, it may also involve rehabilitation by health professionals such as nurses, occupational therapists, and physiotherapists. This means that the standard treatment or care will vary among participants and municipalities.

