Motivation for rehabilitation	Numeric scale of 1–10, where 1 is low motivation	t1
Main health challenge	The most dominant health problem	t1
Other health challenges	Presence of additional health problem(s), yes/no	t1
Health status	Changes in health status in last 10 weeks, 3.5 months, and 6 months, respectively: yes/no	t2, t3, t4
Health care services and cost measures		
Warranted community-based assistance	*Frequency and type of assistance required*	t1
	Home help/Nurse/Auxiliary nurse/Occupational therapist/Physiotherapist/Mental health service/Meals on Wheels/Other assistance/No assistance	
Inpatient and outpatient treatment since last assessment	*Frequency and type of cointerventions*	t2, t3, t4
	Hospital admissions/Admissions to other institutions/Day center placement/Outpatient treatment	
Current home-based assistance offered	*Presence and frequency of home-based assistance*	t2, t3, t4
	Home help/Nurse/Auxiliary nurse/Occupational therapist/Physiotherapist/Mental health service/Meals on Wheels/No assistance	
Current community institution-based service offered	*Type of institution-based service offered*	t2, t3, t4
	Nursing home placement long-term/Nursing home placement short-term/Day placement/Other institution placement/No institution placement	
Usage of home-based services	*Weekly time registration (in minutes) of working time during home visits*	t5
	Home help/Nurse/Auxiliary nurse/Occupational therapist/Physiotherapist/Social educator/Assistant/Student/Other	

t1 = baseline assessment, t2 = 10 weeks after baseline assessment, t3 = 6 months after baseline assessment, t4 = 12 months after baseline assessment, and t5 = daily assessment during 6 months after baseline assessment

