### Sample size calculation

In an earlier study performed with older adults, the standard deviation for the primary outcome was shown to be 1.4 for COPM performance and 1.6 for COPM satisfaction [33]. The current trial is a multicenter study with 44 participating municipalities, so we expect that the variation in the COPM scores will be larger, and thus we employ a conservative estimate of 2.5 for the standard deviation. Furthermore, the allocation of participants to the intervention group or control group will not be randomized, and the number of participants in the intervention group will probably be three to four times that in the control group. We aim to detect a change of one point as statistically significant at a two-sided 5 % level and with a power of 80 %. Based on these estimates, sample size calculations indicate that we need to include 70 participants in the control group and 260 in the intervention group. Therefore, to consider the possibility of a relatively high dropout rate (up to 35 %) due to frail participants, a minimum of 107 and 400 participants will be included in the control and intervention groups, respectively.

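### With non-randomised groups, neither eligibility nor the baseline form captures time since decline or services already received, so natural recovery could be mistaken for, or could mask, a reablement effect

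*Protocol article*

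**What the plan says.** The section on participants and eligibility criteria gives one inclusion rule for both groups: "People will be eligible if they are home-dwelling, over 18 years of age, understand Norwegian, and have experienced a functional decline". The exclusions are: "Participants will be excluded if they are in need of institution-based rehabilitation or nursing home placement, terminally ill, or cognitively reduced". Neither sentence refers to when the decline occurred, to a new application or referral, or to home services already in place.

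The two treatments have different time structures. For reablement, "In general, the intervention lasts for a period of 3–10 weeks", and the baseline COPM interview supplies the goals around which the episode is planned. For the control group, "the standard treatment will not be time limited and thus it may continue after 10 weeks", and "the content of the compensating help will be delivered according to the applications made by the participants". The article does not say whether that application must be new.

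The sample size section states that "the allocation of participants to the intervention group or control group will not be randomized". The Discussion accepts that this weakens causal inference. It proposes to compare baseline levels, treats comparable levels as grounds for crediting later differences to reablement, and says that any initial differences may be controlled in the analysis.

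Table 2 lists, at baseline, the type and frequency of community-based assistance warranted, the main health challenge and whether there are other health challenges. Change in health status, current home-based assistance and the item "Inpatient and outpatient treatment since last assessment" are listed only at 10 weeks, 6 months and 12 months.

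**The concern.** In a randomised trial a broad entry rule affects both groups alike. Here group membership follows the municipality or zone, and the two treatments have different natural starting points. A reablement participant is assessed just before a planned episode begins. A control participant may be a new applicant, but the stated rule would equally admit someone who has had stable home help for a long time, with baseline falling at an arbitrary point in that care.

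People whose decline is recent may tend to improve without treatment, and people with long-standing decline may tend to stay level or worsen. If the groups differ in this mix, the 10-week changes in COPM, physical performance and EQ-5D, and the service-use and cost comparison, would differ for reasons other than reablement. The comparison of baseline levels would not detect it, because two people with the same COPM score can be on different courses.

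**Working it through.** **What the documents settle**

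1. *Eligibility.* The inclusion and exclusion sentences contain no recency, new-application or prior-service condition, and no other part of the article supplies one.
2. *Start of follow-up.* In the reablement group, baseline precedes an episode of 3 to 10 weeks. In the control group, care is open-ended and follows applications of unstated age. Baseline therefore need not mark the same point in the two groups.
3. *Baseline data.* Required assistance at baseline, by type and frequency and including none, partly separates people by level of need. It does not date the decline, record a recent discharge, or say what was already being received.
4. *Planned analysis.* The fixed-effects model in the analysis of effectiveness removes stable differences between municipalities. A different recovery course among the individuals enrolled is not a stable municipal difference. Adjustment for initial differences is described as optional, and it can use only what was measured.

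**How large a bias could be**

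The plan gives no figure for this, so only an illustration is possible.

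Inputs from the sample size section: SD 2.5; 70 control and 260 intervention participants analysed; target difference 1 point; two-sided 5% level. The usual two-means formula at 80% power gives 63 and 234 at this ratio. The plan's 70 and 260 are therefore conservative (power 84.4% by the same formula). That mismatch has no bearing on this point.

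SE = 2.5 × √(1/260 + 1/70) = 0.337, ignoring clustering by municipality.

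Assumptions, not from the documents:
- the share with recent decline differs between groups by 20 to 40 percentage points;
- recent decliners gain 0.5 to 1.5 COPM points more than others without treatment.

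Bias = difference in share × extra untreated gain, which runs from 0.2 × 0.5 = 0.1 to 0.4 × 1.5 = 0.6 points.

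With no true effect, the chance of a significant result is 1 − Φ(1.96 − bias/SE) + Φ(−1.96 − bias/SE):

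| Bias (points) | Bias/SE | Chance of a significant result |
|---|---|---|
| 0 | 0 | 5% |
| 0.1 | 0.30 | 6.0% |
| 0.2 | 0.59 | 9.1% |
| 0.4 | 1.19 | 22.1% |
| 0.6 | 1.78 | 43.0% |

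The same imbalance in the other direction would mask an effect. With a true difference of 1 point, the apparent difference would be 0.9 to 0.4 points. Power would fall from 84.4% to about 76% (0.9/0.337 = 2.67) or 22% (0.4/0.337 = 1.19).

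**The case against.** The strongest reply is that the imbalance is supposed, not documented. Nothing says that controls are long-term users or that reablement participants declined recently. Control help is tied to applications, so some or all controls may be new. The same broad rule would admit a long-standing home-help user in a reablement municipality. This stands. A reader might infer that natural recovery *is* counted as a reablement effect and that the bias favours reablement; the text supports neither statement.

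A reader might also infer that statistical adjustment is impossible. That is too strong: required assistance, main health challenge and the baseline outcome scores allow partial adjustment. The absence of a baseline entry for inpatient and outpatient treatment is also not an error in itself, because that item is defined as the period since the previous assessment.

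The article is a condensed document. Recruitment instructions may sit in the full protocol or in the evaluation pack given to each municipality, and the flow diagram was not available for this review. If those sources already fix the entry point or collect these items, the concern falls away to that extent. However, Table 2 is presented as the summary of measures to be collected, and it does not list them.

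Finally, the authors openly acknowledge the lack of randomisation and value the natural setting. That is fair, and it argues against narrowing eligibility. It does not answer the point that a comparison of baseline levels cannot show a difference in time since decline.

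**Conclusion.** The point holds as a possible and, on the listed measures, largely undetectable source of confounding. It is not a demonstrated bias. The documents establish three things: the entry rule leaves recency and prior services open, the starting point of follow-up need not match between groups, and the baseline measures capture this only in part. The Discussion's inference from comparable baseline levels is therefore less secure than it is made to appear.

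The direction is not fixed by the documents and the size is unknown. The range of 0.1 to 0.6 COPM points, with false-positive rates of about 6% to 43%, rests entirely on the two assumptions stated above and on an SE that ignores clustering. At the low end the effect on error rates is slight; at the high end the bias exceeds half of the 1-point target. Zero or reversed imbalance is also possible. The change is worth making because it is cheap, not because the trial is shown to be biased.

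**What to change.** Add to the baseline form, in both groups:
- approximate time since the functional decline;
- any discharge from a hospital or other institution within a fixed recent period, chosen in advance;
- home services already received, and whether the current application is new.

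Report these items by group and name them in advance as covariates in the primary between-group model. Add a sensitivity analysis limited to participants with a new application. Where possible, complete the baseline assessment in both groups before the first visit under the current application.

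The cost is a few more baseline items and some imprecision in recalled onset, so residual confounding will remain.

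Restricting eligibility or the main analysis to new applicants is a more debatable step. At three to four intervention participants per control, 750 participants give about 188 (750/4) to 150 (750/5) controls. Under the 40-point assumption at least 40% of controls would not be recent decliners. If those same people were the ones excluded, at most about 112 to 90 would remain, against the stated minimum of 107. Such a restriction would also give up some generalisability and replace the stated analysis population. Adjustment plus a sensitivity analysis avoids both losses.

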### Interventions

#### Reablement

Reablement is an intensive, interdisciplinary intervention. In general, the intervention lasts for a period of 3–10 weeks. To enable and enhance activity performance, it is crucial to acknowledge that the person is the expert on her/his own life. The main focus is to establish a dialog to identify activities that the individual perceives as meaningful to work on or to improve. The intervention is targeted to achieving these activity goals. Therefore, the patient-specific Canadian Occupational Performance Measure (COPM) will be used as part of the baseline assessments to give directions for the modeling of the reablement intervention. The COPM interview and scoring start with the following question: “What are the most important activities in your life now?” During the COPM assessment, the participant will define up to five activity goals that are essential to her or him. Based on these goals, a rehabilitation plan will be developed to promote a match between the activities and goals identified by participants, and professional initiatives. Intensive attention will be given to encourage participation and stimulate daily training for the participants, including performing their daily tasks. Individual tailoring is a major principle of reablement, so the content of the intervention will vary among participants, although the basic features are the same. Table 1 gives an overview of the content of the intervention, including fundamental principles and key components.

**Table 1 Tab1:** Content of the reablement intervention

Fundamental principles	Process, key components
• The rehabilitation period will be a maximum of 10 weeks.	• *Training in daily activities* such as personal hygiene, climbing stairs, family visits, cleaning the house, being able to write, or walking indoors/outdoors.
• A person-centered, resource-oriented, and interdisciplinary approach will be applied.	
• An occupational therapist, physiotherapist, nurse, or social educator will conduct an interview using the Canadian Occupational Performance Measure to identify activity limitations and participation restrictions. Based on the identified activity goals, a rehabilitation plan will be developed together with the participant. Next, an integrated multidisciplinary team with shared goals will collaborate with the participant throughout the whole rehabilitation period.	Optimizing performance through intervention components such as adaptations of activities and the environment.
	• *Exercise programs* such as performing exercises to improve strength, balance, or fine motor skills. The exercises will be incorporated into daily routines and the participant will be encouraged to train on their own.
• The rehabilitation will involve repetitive training and multiple home visits by health care personnel, who will be present during daily training to build confidence and relearn skills.	
• All health care personnel will stimulate the participant in self-management and self-training.	

